### Measurements

Background information from the Swedish Quality Register for Pain Rehabilitation (SQRP) (http://www.ucr.uu.se/nrs/). Information about medication, possible trauma and background information and degree of sick leave will be obtained from the medical record.

#### Questionnaires from SQRP

EuroQoL five dimensions questionnaire^55^Hospital Anxiety and Depression Scale^56^Insomnia Severity Index^57^Multidimensional Pain Inventory^58^Screening on physical activity by the National Board of Health and Welfare.^59^

#### Other questionnaires

VAS-f before and after neuropsychological assessment^31^VAS-f and pain before and after the fMRI scanningMFI-20^60^Pain level, experienced during the neuropsychological examination, will be rated (0–10) at the end of the session.

#### Neuropsychological tests

WAIS-III Digit-Symbol-Coding (Coding) measures psychomotor speed and incidental memory. The higher values the better results.^61^ The Coding subtest from WAIS-III will be used instead of WAIS-IV as the former has been validated for measuring fatigability.^33 42^WAIS-IV Matrix reasoning measures logical reasoning and premorbid cognitive level. The higher values the better results.^62^WAIS-IV Digit Span measures verbal attention span and working memory. The higher values the better results.^63 64^Delis-Kaplan Executive Function Scale Color-Word Test and Word Fluency Test measure different aspects of executive functioning. For the Color-Word test, lower values represent better results and for the Word Fluency Test, higher values represent better results.^65^Ruff 2 & 7 measures automatic visual scanning and complex selective attention and processing speed. The higher values the better results.^66^MapCog Spectra is a newly developed attention test that is administered via an iPad. The MapCog test records and analyses the occurrence and frequency of attentional lapses and compares these to standardised norms. The standardisation is based on a healthy reference group, n=313, aged 8–87 years. The test has a sensitivity of 95.8% and a specificity of 96% for identifying individuals with attention deficit disorder. The test is easy to perform (5–10 min), the data processing is automatic, the results are objective and there are no learning effects. The lower values the better results.^67^ We also measure fatigability by comparing the results at the end of the test with the beginning of the test.

For all tests, mainly raw score scores will be used in the analysis.

### Primary outcome variables

The outcome variables are summarised in table 1.

**Table 1 T1:** Outcome measures

Primary outcome measures	Description
1. Fatigability from WAIS-III Coding	The subject must fill in the blank spaces with the symbol which is paired to the number during 120 s. Cognitive fatigue is assessed by subtracting the number of digits produced in the first 30 s from the number of digits produced in the last 30 s during the full 120 s period. A non-ascending score (<0) is considered an indicator of cognitive fatigue. Both the total value and the difference between the production between 0–30 s and 91–120 s are measured, and a dichotomised variable (non-ascending value) will be used.
2. D-KEFS Color-Word Test	Inhibition of over-learnt verbal responses. The test has four conditions: (1) naming colours (red, blue, or green, (2) reading colour words printed in black, (3) naming the colour of the words red, blue, or green written in a different colour than is the written word, which means inhibition of an over-learnt function of reading the word; (4) repeatedly switching between naming colours and reading out the printed words as quickly as possible, while at the same time, the person needs to keep track of clues that indicate rule change. Contrast scores are used to examine the performance of the more complex tasks 3 and 4 and the basic tasks 1 and 2. Faster time represents a better result.
3. Fatigability on e-prime vigilance task in the fMRI scanner	The participants are instructed to push a button as quickly as they can when a set of four zeroes appears in a red rectangle and do nothing if other numbers appear. After each response, visual feedback of the reaction time is displayed. If the participant reacts to a false stimulus or if the response time exceeds 1 s the feedback ‘false answer’ or ‘no answer’ is displayed. The stimuli are presented at random intervals. The results are divided into quintiles and the mean reaction time is calculated for each quintile.
4. Task-fMRI	BOLD signal changes during the e-prime vigilance task.
5. Resting-state fMRI	Changes in functional connectivity after performance of the e-prime vigilance task.
6. Inflammatory markers	Omics analyses will be used in this study. Omics studies are mainly exploratory and hypothesis-generating, that is, which proteins, metabolites, and lipoproteins are identified cannot be determined in advance. Exploratory targeted analyses using panels of cytokines and chemokines and neuroinflammation will be used in combination with omics.
Secondary outcome measures	Description
1. MFI-20	The MFI-20 consists of five scales, based on different modes of expressing fatigue. Each scale contains four items for which the person has to indicate on a seven-point scale to what extent the particular statement applies best. 'General fatigue' includes general statements concerning a person’s functioning. 'Physical fatigue' refers to the physical sensation related to the feeling of tiredness. 'Reduced activities' measures reduction in activities and 'Reduced motivation' is lack of motivation. 'Mental fatigue' measures cognitive symptoms related to fatigue. Some sentences are inverted and need to be rescored. On each scale, higher values represent higher levels of fatigue.
2. Visual Analog Scale of Fatigue	Measurement of self-rated current fatigue level. Ranges from 0 (corresponding to no fatigue) to 100 millimetres (corresponding to the worst possible fatigue).
3. D-KEFS Word Fluency Test	The test measures expressive language skills, initiative, and working memory and consists of three different conditions: verbal phonological fluency^1^ where the test person for 60 s produces as many unique words as possible that begin with a given letter; category fluency^2^ where the test person for 60 s per category produces as many unique words as possible in two given semantic categories and; category change fluency^3^ where the test person produces as many unique words as possible in 60 s and switches between two specified semantic categories every other time. The more words, the better performance.
4. WAIS-IV Digit Span forward and backward repetition (Attention span and working memory)	The test person must repeat numbers that the leader reads out. The number of digits is increased by one unit every two times. The test person repeats the numbers in the same order (forward repetition) or reverse order (backward repetition). Forward repetition measures auditory attention span and short-term memory, while backward repetition measures auditory working memory. Both the total number of digits and the difference between forward and backward repetition are measured.

BOLD, Blood-Oxygen-Level Dependent; Coding, Digit-Symbol Coding Test; D-KEFS, Delis-Kaplan Executive Function Scale; fMRI, functional MRI; MFI, Multidimensional Fatigue Inventory; WAIS, Wechsler Adult Intelligence Scale.

## Data collection and management

### Recruitment

The pain rehabilitation unit at the Department of Rehabilitation Medicine at Danderyd University Hospital and the Department of Pain Rehabilitation, Pain Center at Umeå University Hospital offer team assessment and evidence-based team-based multimodal rehabilitation for patients with complex CP (>3 months). To receive rehabilitation at the clinics, a referral including a pain assessment is required. Information about the study is sent to the referred patients at the same time as the call for the initial assessment.

At the time of the team assessment, the patient is asked orally by the team nurse if the testing psychologist may contact the patient to inform them about the study. The patient’s consent is logged, and a log is made of the number who say yes and the number and gender and age of those who say no. No personal data other than gender and age will be registered for those who say no. The purpose of the log is only to be able to assess generalisability based on the proportion who have agreed to participate in the study.

The testing psychologist then calls the patients and inform them about the study and if the patient agrees, an appointment is made for neuropsychological assessment. In connection with the assessment, the psychologist ensures that they have understood the information about the study and that participation is voluntary, inquires about whether they have further questions and collects the signed consent form. Female patients who are investigated in Umeå are asked if they want to participate in the fMRI study. The patients are assessed by an independent psychologist, who does not treat the patients clinically.

The study patients will be compared with healthy controls. Healthy controls will be recruited through advertising among hospital staff. Matching on a group level will be done regarding age, gender and level of education.

### Imaging

In a 3-tesla MR scanner, conventional anatomical MRI sequences will be analysed as well as sequences for detailed anatomical assessment. We use an established measurement paradigm that has previously been used on healthy subjects^68^ and patients with mild traumatic brain injury.^69^

All participants are examined with fMRI during a 20 min vigilance (reaction time) task (e-prime), where fatigue is measured by recording mean reaction time/quintile. BOLD resting-state fMRI examination is performed before and after the task. In addition, the MRI protocol will include standard clinical protocols that include high-resolution T1-weighted sequences and high-resolution T2-weighted scan (Fluid-attenuated inversion recovery (FLAIR)). All structural images are reviewed by a radiologist to screen for incidental findings within the brain. The investigation is non-invasive and takes about 60 min.

### Blood sampling

Venous blood samples (10–20 mL) are collected in P100 tubes from BD diagnostic, containing a protease inhibitor cocktail that prevents protein cleavage/degradation from each subject. The blood samples are centrifuged to remove red blood cells. The plasma fraction is transferred to a new tube, portioned and stored at −86°C until analysis at the PAINOMICS lab in Linköping, Sweden.

Plasma samples will be analysed using antibody-based methods such as multiplex technology (Meso Scale Diagnostics, Rockville, MD). Instrument, MSD Technology platform, which is a multiplex instrument, which can analyse up to 92 different substances (cytokines, chemokines, growth factors and metabolic proteins) in one go. Omics analysis consisting of proteomics, metabolomics and lipoprotein profiling will be used to identify other inflammatory markers than those analysed by the antibody-based (targeted analysis) method.

### Data management

All data materials will be recorded with a participant ID and will be unidentifiable for those who do not have access to the code key. In the statistical processing, the participants will be coded. The code key is stored separately from the data and only pseudonymised data will be shared between the two sites. Deidentified data will be electronically stored on the server at the two sites and will be deleted 10 years after the project has ended. The final data set will be available to researchers actively contributing to statistical analyses and publications. Data entry will be controlled by initial exploratory analyses, including range checks, to promote data quality. Regarding biological specimens, the samples of blood will be centrifuged and plasma will be aliquoted and stored at the Linköping University Hospital, with special notification to the biobank. The samples will be blinded before analysis. This study has an exploratory character as we use proteomic methods, and, therefore, samples (that are not thawed) will be stored for future analysis according to approved ethical application.

### Sample size

Power calculation on the primary fatigue measure, the WAIS-III Coding Test: for a mean difference between patients and controls of 2.5, and SD of 3.0, and an alpha level of 5% (two-sided) and strength of 80%, a group of 24 participants in each group is a sufficiently large sample.^70^ This size also holds for the fMRI substudy as an earlier study on mild traumatic brain injury has shown that 10 patients in each group were sufficient.^45^ The biomarker data will be analysed using multivariate data analysis (MVDA). Algorithms for sample size calculations using MVDA do not exist. MVDA is designed to handle a few subjects, low-to-variable ratios and multiple intercorrelated variables. Based on our previous biomarker study,^48 71^ the sample size in this study will be sufﬁcient to detect a difference between groups.

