#### Participants for fMRI

Twenty-four^24^ patients, women only, between 18 and 45 years with CP and who have undergone a neuropsychological assessment at the Department of Pain Rehabilitation, Pain Center at Umeå University Hospital will also undergo an fMRI investigation. All patients fulfilling the criteria for participation in the fMRI study from Umeå the study site are offered to participate in fMRI scanning and blood sampling, until the participation rate goal^24^ is reached. They will be compared with 22 female controls from the healthy control group.

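### The sample-size section asserts that 24 per group also suffices for the fMRI substudy, but that substudy is 24 v 22 and its adequacy for primary outcomes 3 to 5 is not demonstrated

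*Protocol article*

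**What the plan says.** The Sample size section opens with "Power calculation on the primary fatigue measure, the WAIS-III Coding Test". The inputs are given as "for a mean difference between patients and controls of 2.5, and SD of 3.0", with "an alpha level of 5% (two-sided) and strength of 80" per cent, and the conclusion is that "a group of 24 participants in each group is a sufficiently large sample".

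The next sentence carries this number over to imaging: "This size also holds for the fMRI substudy as an earlier study on mild traumatic brain injury". The finding credited to that earlier work is that "10 patients in each group were sufficient". The article does not say what was measured in it, how large the effect was, or in what sense 10 per group sufficed.

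The Abstract and the section Participants for fMRI fix the substudy at 24 female patients. Of these patients the latter section says: "They will be compared with 22 female controls from the healthy control group".

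Table 1 lists three primary outcomes that are measured only in this substudy: fatigability on the vigilance task in the scanner (outcome 3), BOLD change during the task (outcome 4) and change in functional connectivity after the task (outcome 5). Study design describes the whole study as explorative.

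**The concern.** The sentence makes a positive claim of adequacy, so this is not a detail that a condensed article has merely left out. Two things in it do not fit.

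First, the size it refers to is 24 in each group, and the substudy does not have 24 controls.

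Second, the reasoning does not reach the imaging outcomes. A size computed from a difference on a paper-and-pencil test carries no information about the spread or likely difference in reaction-time decline, BOLD signal or connectivity. The only bridge is the statement about 10 per group in mild traumatic brain injury. The Introduction itself treats it as an open question whether the patterns seen in brain injury also appear in patients with pain and fatigue, so carry-over from that population cannot also be the justification.

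Half of the primary outcomes depend on this sentence. A reader who accepts it may take a non-significant imaging result in 46 women (24 + 22) as evidence that there is no difference.

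**Working it through.** **Inputs from the Sample size section:** difference 2.5, SD 3.0, two-sided alpha 0.05, power 80%, 24 per group. **From the Abstract and Participants for fMRI:** 24 patients, 22 controls. **Not given:** an effect size or SD for outcomes 3 to 5. Any effect size used for them below is an assumption.

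**Step 1: reproduce the plan's figure.** The standardised difference is d = 2.5/3.0 = 0.833. The normal approximation is

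n = 2 × (1.960 + 0.842)² × (3.0/2.5)² ≈ 2 × 7.85 × 1.44 ≈ 22.6, so 23 per group.

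The exact calculation uses the noncentral t distribution with n1 + n2 − 2 degrees of freedom and noncentrality d × √(n1·n2/(n1 + n2)). It gives 24 per group: noncentrality 0.833 × √12 = 2.89, 46 degrees of freedom, power 80.7%. The stated 24 is correct for Coding.

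**Step 2: the actual substudy size at the same effect.** For 24 v 22 the noncentrality is 0.833 × √(24 × 22/46) = 0.833 × 3.388 = 2.82, with 44 degrees of freedom.

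| Groups | Exact power at d = 0.833 | d for 80% power |
|---|---|---|
| 24 v 24 | 80.7% | 0.83 |
| 24 v 22 | 78.9% | 0.85 |
| 10 v 10 | 42.2% | 1.32 |

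Having two fewer controls costs 80.7 − 78.9 = 1.8 percentage points.

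**Step 3: what 24 v 22 offers for an imaging outcome, over a range of assumed effects.** This treats the outcome as one number per person, compared between groups by a two-sided 5% t-test.

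| Assumed d | Exact power, 24 v 22 |
|---|---|
| 0.5 | 38% |
| 0.6 | 51% |
| 0.7 | 64% |
| 0.8 | 75% |
| 1.0 | 91% |

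The article states no multiplicity correction for these outcomes. If alpha were divided by 3 (assumed), power at d = 0.833 would be 63%; if divided by 6 (assumed), 53%.

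**Step 4: what the 10-per-group benchmark can carry.** With 10 per group, a two-sided 5% t-test reaches significance only if the observed |d| is at least 2.101 × √(2/10) = 0.94. At the plan's own planning effect such a study has 42% power. A statement that 10 per group sufficed can therefore support 24 v 22 only together with the effect it refers to. If that effect was about 1.32 SD, where 10 v 10 has 80% power, then 24 v 22 has 99%. If the effect in chronic pain is 0.5 SD, 24 v 22 has 38%. The article gives nothing with which to choose between these.

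**The case against.** The strongest reply is that the protocol's benchmark is 10 per group, and 24 and 22 are both more than double it. The cited study cannot be seen here. It may report a power calculation or a within-person design, and under a large effect the substudy would be very well powered. The study is labelled explorative, the small control group is already listed among the limitations, and a detailed imaging justification may stand in the full protocol. The planned analyses (independent components, dual regression, general linear modelling, scans before and after the task) are also not a single two-sample t-test, so the figures in Step 3 are only a guide.

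Much of this stands, and it rules out three stronger readings that a reader might infer:

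- *The substudy is underpowered, or its promised adequacy is not delivered.* Without an effect size for outcomes 3 to 5 this cannot be computed. The documents support only that adequacy is not demonstrated.
- *The missing two controls undermine the sample.* They cost about 2 percentage points. This is a loose reference to 24 per group, not a material loss, and the counts agree wherever the substudy is described.
- *Any effect reported from 10 per group must be an overestimate.* Selection on significance inflates effects on average, and strongly when the true effect is modest. It does not do so in every case, and the article does not say what kind of result the earlier study gave.

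The reply does not rescue the sentence itself. An exploratory study need not have power for imaging outcomes, but this one lists them as primary and says that the size holds for them, on grounds that do not show it.

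**Conclusion.** The point holds as a claim without support. The 24 per group is right for WAIS-III Coding and for nothing else in the section. Applied to the fMRI substudy, it gives the wrong control count (22, not 24; minor) and asserts adequacy for three of six primary outcomes without an effect size, SD or power for any of them (the main defect).

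The indicative size is 80% power at 0.85 SD and about 38% at an assumed 0.5 SD. This assumes one scalar outcome, a two-group t-test, no missing scans and no multiplicity correction; losses or a correction would lower the power. According to Study setting, data collection is complete but no analyses have been completed and reported, so the statement can still be corrected before results appear.

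**What to change.** In the Sample size section, delete the sentence extending the Coding-based size to the fMRI substudy, including its 10-per-group argument. Replace it with text such as:

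> The fMRI substudy compares 24 patients with 22 controls. No separate power calculation was made for the imaging outcomes. For a single two-sided 5% two-group comparison this size gives 80% power for a standardised difference of about 0.85 (about 38% power at 0.5), and less after any multiplicity correction. Imaging group differences will be reported with interval estimates where applicable, and non-significant results will not be interpreted as evidence of no difference.

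The authors should confirm the second sentence. If a calculation for an imaging outcome exists, its outcome, effect size, SD and power should be given instead. The new text should not say that the substudy was sized by feasibility: the article does not say so, and Strengths and limitations says that the control group's size was adapted to the fMRI and blood-sampling comparisons.

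The cost is one reworded passage and a less favourable statement about the imaging part. No patients, scans or analyses are added.

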### Confidentiality

Information on participants will be handled by healthcare professionals adhering to Swedish Law ensuring confidentiality and data protection by coding individual participants’ collected data. Results and data will be presented at a group level in publications, rendering the identification of individual patients impossible. All data will be stored in accordance with the General Data Protection Regulation. The data for participants from the Stockholm area will be stored in a password-protected project server at Danderyd University Hospital and for patients from the Umeå region at Umeå University. Data will not be accessed by unauthorised persons.

### Data analysis

For all study questions, descriptive statistics will be used to depict demographics, injury characteristics, results on neuropsychological tests and psychological screening instruments. Multiple linear and logistic regression will be used to detect any interaction effects. Parametric methods such as independent t test, one-sample t test (comparing with standardised test norms), Pearson correlation and multiple linear regression) will be used when data are normally distributed and non-parametric methods (Man-Whitney U-test, Spearman correlation, χ^2^, logistic regression) when data are skewed or on interval level or lower. Missing data will be listed as data loss. The significance level will be set to <0.05 (two-tailed).

Concerning study question 4, data from omics and targeted analysis will be analysed using advanced MVDA using SIMCA-P+. This is the recommended method in omics since it accounts for multicollinearity problems and missing data when the number of variables exceeds the number of observations.^72^ MVDA will be used for the analysis of the biomarkers. Principal component analysis (PCA), orthogonal partial least squares- discriminant analysis (OPLS-DA) and OPLS regression will be applied for analysis of the biomarkers and their ability to differentiate between groups and their correlation with clinical characteristics and outcomes. PCA is an unsupervised analysis that reduces the dimensionality of data and extracts and displays systematic variation in the data matrix. Outliers will be identified using score plots in combination with Hotelling’s T2 test (the distance from the origin in the model plane for each selected observation) and DModX (the distance of the observation to the X model plane). The values that are larger than the 95% confidence limit are considered suspicious and the values larger than the 99% limit should be considered strong outliers.^73^

OPLS-DA will be used to identify biomarkers responsible for group separation. The OPLS-DA model reveals variables as loadings and the higher the value of a loading, the more important it is for the model, for example, group separation. This can be measured as a variable influence on projection (VIP) values. The p(corr) is the loading of each variable scaled as a correlation coefficient (ranging from −1 to +1). An absolute p(corr) of >0.4–0.5 and VIP >1.0 are considered significant.^72^ Another model diagnosis parameters that are considered are R2 value—which describes the ‘goodness of fit’, that is, the fraction of the sum of squares of all the variables explained by a principal component. The Q2 value describes the ‘goodness of prediction’, that is, the fraction of the total variation of the variables that can be predicted by a principal component using a cross-validation method^73^ and cross-validated analysis of variance (CV-ANOVA). The R2 must not differ more than 0.2–0.3 compared with Q2 and CV-ANOVA <0.05 is considered a significant model.

Regarding study question 5 analysis of fMRI data will be done with special software for MRI analysis, developed at Oxford University (http://www.fmrib.ox.ac.uk/fsl/). The resting state data will be analysed using FSL (http://www.fmrib.ox.ac.uk/fsl) tools such as MELODIC to identify spatial and temporal components by independent component analysis at the group level. All relevant preprocessing steps will be performed, such as motion correction, registration to a standard template and filtering of low-frequency drifts. Group differences between patients and controls will be analysed using FSL dual regression. The fMRI data will be analysed using both MELODIC and FEAT, which is an FSL tool based on general linear modelling performing multiple regression on the fMRI data and the functional paradigm.

For study question 6, multiple linear and logistic regression will be used to detect any interaction effects.

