### Participants

#### Patients for neuropsychological assessment

Two hundred outpatients between 18 and 50 years with CP from the Unit of Pain Rehabilitation at the Department of Rehabilitation Medicine at Danderyd University Hospital or from the Department of Pain Rehabilitation, Pain Center at Umeå University Hospital will be included. There will be no stratification of age, but the majority of the patients will be women as they are over-represented among those receiving rehabilitation for CP. In the analyses, the patients are compared with 36 healthy controls.

Please see the flowchart for an overview of the study (figure 1).

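### For 200 patients against 36 controls the plan leaves the variance form of the t test open; naming Welch's test (and HC3 errors in the matching linear regressions) protects the 5% level at very low cost

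*Protocol article*

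**What the plan says.** All references are to the protocol article.

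- **Data analysis.** The section names "Parametric methods such as independent t test", the one-sample t test, Pearson correlation and multiple linear regression. The rule for choosing them is that they "will be used when data are normally distributed and non-parametric methods" otherwise. It sets no condition on equal variances and does not mention a pooled, Student or Welch form. The test level is 0.05, two-tailed.
- **Patients for neuropsychological assessment.** The patient group is "Two hundred outpatients between 18 and 50 years with CP", and "In the analyses, the patients are compared with 36 healthy controls".
- **Sample size.** The calculation for WAIS-III Coding is "for a mean difference between patients and controls of 2.5, and SD of 3.0", two-sided 5% and 80% power, giving 24 per group. One SD serves both groups.
- **Participants for blood sampling / for fMRI.** These comparisons are 36 v 36 and 24 v 22.
- **Study setting.** Data collection is finished, and no analyses have yet been completed and reported.

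**The concern.** The equal-variance t test estimates one common variance, and with 200 v 36 that estimate is almost entirely the patients'. The uncertainty of the difference, however, comes mainly from the 36 controls. If the two SDs differ, the standard error is wrong: too small when controls vary more, too large when patients vary more. A normality check does not detect this.

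Unequal SDs are plausible here. Patients are consecutive clinical referrals at two sites. Controls come from hospital staff and their circle and are matched only at group level. The p value and confidence interval for the first study question (do patients show more fatigue than controls?) would be affected. So would the patient–control coefficient in a linear regression with conventional standard errors.

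**Working it through.** **1. The plan's own figure.** Inputs from the sample size section: difference 2.5, SD 3.0, two-sided 5%, power 80%, equal groups. The normal approximation gives 2 × (1.960 + 0.842)² × (3.0/2.5)² = 22.6, so 23 per group. The exact noncentral t calculation gives power 0.789 at 23 and 0.807 at 24. The stated 24 is reproduced. That design is balanced; the comparison to be analysed is not.

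**2. Why imbalance matters.** Let r be the patient SD divided by the control SD, with the control SD set to 1. The documents do not give r; the range below is assumed.

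- Variance assumed by the pooled test: [(199 r² + 35)/234] × (1/200 + 1/36)
- True variance: r²/200 + 1/36
- Approximate size: 2 × [1 − Φ(1.970 × √(assumed/true))], where 1.970 is the t critical value on 234 degrees of freedom

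For r = 0.8: assumed 0.6938 × 0.032778 = 0.02274; true 0.0032 + 0.02778 = 0.03098; √(0.02274/0.03098) = 0.857; size 0.091.

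For r = 1.5: assumed 2.063 × 0.032778 = 0.06762; true 0.01125 + 0.02778 = 0.03903; √(0.06762/0.03903) = 1.316; size 0.0095.

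**3. Simulated type I error at 200 v 36** (normal data, 400,000 samples per row, nominal 5%):

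| r (assumed) | Pooled, formula | Pooled, simulated | Welch, simulated |
|---|---|---|---|
| 0.67 | 13.5% | 13.6% | 5.0% |
| 0.8 | 9.1% | 9.3% | 5.0% |
| 0.9 | 6.7% | 6.8% | 5.0% |
| 1.0 | 4.9% | 5.0% | 5.0% |
| 1.1 | 3.5% | 3.6% | 5.0% |
| 1.25 | 2.2% | 2.3% | 5.0% |
| 1.5 | 1.0% | 1.0% | 5.0% |
| 2.0 | 0.2% | 0.2% | 5.0% |

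**4. Power at 200 v 36, control SD 3.0:**

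| Patient SD | Difference | Pooled | Welch |
|---|---|---|---|
| 4.5 (assumed) | 1.5 (assumed) | 48% | 70% |
| 4.5 (assumed) | 2.5 (planned) | 95% | 99% |
| 3.0 (planned) | 2.5 (planned) | 99.6% | 99.5% |

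**5. Cost of Welch when the SDs are equal (both 3.0).** Power lost against the pooled test is 1.2 points at a difference of 1.0, 1.4 at 1.25, 1.3 at 1.53, 1.0 at 1.75, 0.6 at 2.0 and 0.1 at 2.5.

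**6. Linear regression.** Least squares with a group term and one normal covariate at 200 v 36 (40,000 samples per ratio) gave type I errors for the group term of 13.7%, 9.3%, 2.2% and 1.1% with conventional standard errors, at r = 0.67, 0.8, 1.25 and 1.5. HC3 standard errors gave 5.3%, 5.1%, 4.8% and 5.0%.

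**7. The near-balanced comparisons.** Over r = 0.5 to 2, the pooled test's size is 5.0% to 5.1% at 36 v 36 and 4.6% to 5.9% at 24 v 22.

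**The case against.** The strongest reply is that the article never specifies an equal-variance test. The word independent separates the test from the one-sample t test listed beside it, the list is illustrative, and a condensed article may leave the variance form to a fuller plan. **This stands:** a reader might infer that the plan prescribes the pooled test, but the text does not say so. Nor does the single SD of 3.0 show it, since that is a planning input for 24 v 24, where the two forms nearly coincide.

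Second, the SD ratios come from outside the documents. **This also stands.** A reader might infer that false positives are inflated, but the documents give no direction. The natural argument, a mixed clinical group against selected controls, points to more variable patients, and then the pooled test is conservative.

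Third, at the planned difference of 2.5 the power loss is small: 95% v 99% even with SDs of 4.5 and 3.0. **True.** A reading that the planned comparison becomes underpowered is not supported. The loss concerns smaller effects, and the calibration of p values and intervals remains at issue.

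Fourth, skewed data go to rank tests, and Coding fatigability is also dichotomised. So the t test is only one route. But it is a named route, linear regression is another, and the rank test is no remedy. With equal means and SD ratios of 0.67, 0.8, 1.25 and 1.5, a further simulation put Mann-Whitney rejections at 9.0%, 7.0%, 3.5% and 2.1%.

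**Conclusion.** The point holds as a cheap improvement, not as the correction of a demonstrated error. The plan ties its parametric methods to normality alone and leaves open the one feature on which validity at 200 v 36 depends. If the equal-variance form is used, a 20% difference in SD is enough to move a nominal 5% test to about 9% or, with the opposite ordering, to about 2% to 3%. Welch's test holds 5% in every case examined.

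The figures assume normal data, full recruitment of 200 and 36, and SD ratios that the documents do not supply. It would be too strong to call the change free: the cost is small but not zero. It would also be too strong to extend it to every patient–control comparison, because the blood-sampling and fMRI groups are close to balanced.

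**What to change.** Add one sentence to the data analysis section: mean comparisons of the 200 patients with the 36 controls use Welch's t test, and linear regressions containing the patient–control term use heteroscedasticity-robust (HC3) standard errors.

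Leave the 36 v 36 and 24 v 22 comparisons and the logistic models as they are. Fix the wording before the analyses are run; choosing the form after seeing the two SDs would make the choice depend on the data. No new data are needed. The statistical price is the power loss set out in step 5 of the working, and it arises only if the SDs turn out equal or nearly so.
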